### Statistical analysis

In this experiment, the superiority trial design is adopted. Full analysis set (FAS) included all children who were randomized, received at least one spray of medication, and had at least one visit record. Per-protocol set (PPS) includes only patients who fulfill the protocol. All subjects who have taken the experimental drug will have their data covered by the safety set (SS) if the safety results are recorded. FAS and PPS are selected for effectiveness evaluation, and SS is selected for safety evaluation. If there are missing values in the primary outcome, the method of carrying forward the last observation data to the final results of the trial is adopted. An independent statistician will use SAS v 9.2 for statistical analysis. All hypothesis tests are conducted by two-sided test, and the overall comparison inspection level is 0.05 of α.

Survival data will be statistically described by median, upper quartile, lower quartile survival time, and 95% confidence interval (95% CI), and survival curve will be made. The comparison between groups is checked by log-rank test. If the influence of baseline factors is considered, Cox regression analysis is adopted. For quantitative data, the number of cases, mean, standard deviation, minimum, median, maximum, upper quartile, lower quartile, and 95% CI are used to describe the data. *T* test or paired *t* test is used for statistical analysis of data before and after treatment in two groups or within groups. If the influence of center or other confounding factors are considered, analysis of covariance is used.

For qualitative data, frequency table, percentage, or composition ratio is used to describe the data. For statistical analysis of data before and after treatment in two groups or within groups, *χ*^2^ test, Fisher’s exact probability method, Wilcoxon rank sum test, or Wilcoxon’s sign rank sum test is used. For the comparison of two categories and ranked data, if the influence of center or other factors are considered, CMHχ^2^ test is adopted. If the influence of confounding factors is considered, logistic regression analysis is adopted.

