### Outcome measures

#### Primary outcome

The primary outcome is the time of analgesic onset. Analgesic onset is based on WBS score of sore throat (swallowing pain, same below) intensity, and defined as the reduction of WBS score ≥ 1 grade after the first dose. The WBS uses 6 different faces from smile to crying to describe the pain intensity of children aged 3 and above, from no hurt (0 point) to hurts worst (10 point), with a 2-point interval. It does not need specific cultural background, is easy to grasp, and has a good correlation with other commonly used scales [17, 18]. Children will be asked to swallow and to choose an expression to show how much their throat hurts now. In order to obtain the data of primary outcome, the children will be evaluated 12 times for WBS score (baseline and 5, 10, 20, 30, 40, 50, 60, 90, 120, 150, and 180 min after the first dose) by researchers in the hospital.

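### Last observation carried forward is the stated rule for missing values in a time-to-onset primary outcome; it counts a child lost before onset as observed without relief to 180 min, where censoring at the last score belongs

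*Protocol article*

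**What the plan says.** The Primary outcome section states: "The primary outcome is the time of analgesic onset". Onset is "defined as the reduction of WBS score ≥ 1 grade after the first dose". Scores are taken at "baseline and 5, 10, 20, 30, 40, 50, 60, 90, 120, 150, and 180 min after the first dose", and this part of the follow-up is done "by researchers in the hospital". There are therefore 11 post-dose assessments, and follow-up for this outcome ends at 180 min.

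The Statistical analysis section treats the outcome as survival data, with medians, quartiles and survival curves. It adds: "The comparison between groups is checked by log-rank test", with Cox regression if baseline factors are considered. For gaps in the primary outcome it gives one rule: "If there are missing values in the primary outcome, the method of carrying forward the last observation data to the final results of the trial". The article does not mention censoring. The efficacy set is defined as follows: "Full analysis set (FAS) included all children who were randomized, received at least one spray of medication, and had at least one visit record".

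The Sample size calculation section assumes median onset of 10 min on KHJS and 20 min on control, and a 10% loss to follow-up. It does not say when in the trial that loss occurs.

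**The concern.** An onset time has no earlier value that could be carried forward. Only the WBS score can be. If a child's last score shows no fall of a grade, carrying it forward produces no onset at every later time point. The child then stays in each later risk set although nobody assessed the child there. Kaplan-Meier and log-rank methods, which the protocol already adopts, handle such a child by removing the child from the risk set after the last score.

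At stake are the primary test and the reported median onset times. The rule is written down for the primary outcome itself, so it is not a detail left open for a statistical analysis plan. A plan that follows the sentence inherits the problem, and a plan that censors contradicts the protocol.

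**Working it through.** The protocol gives no figure for the effect of this rule, so there is none to reproduce. The check has three steps.

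**1. One child.** A child last scored at 10 min without relief belongs to the risk sets at 5 and 10 min. Under the carry-forward rule the child counts in all 11, so 11 − 2 = 9 of them are unobserved. A child lost after onset is unaffected under either rule.

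**2. Median.** Assume exponential onset with true median m, and a share q lost before any post-dose score. The carried-forward curve is S(t) = q + (1 − q)·2^(−t/m). Setting S(t) = 0.5 gives

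t = −(m / ln 2) · ln(1 − 0.5/(1 − q)).

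For q = 10% and m = 10: 1 − 0.5/0.9 = 0.444, ln 0.444 = −0.811, 10/ln 2 = 14.43, so t = 11.7 min. Results against true medians of 10 and 20 min:

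| q | KHJS | Control |
|---|---|---|
| 2% | 10.3 | 20.6 |
| 5% | 10.8 | 21.6 |
| 10% | 11.7 | 23.4 |
| 20% | 14.2 | 28.3 |

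The shift is always upward.

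**3. Log-rank test.** Inputs from the protocol: 120 per arm, the assessment grid to 180 min, two-sided 0.05, and medians of 10 and 20 min (hazard ratio 2 if exponential). Assumptions: exponential onset read on the grid, and loss independent of onset. Loss by 30 min means a last score at 0, 5, 10, 20 or 30 min. Each simulated data set was analysed twice, once carried forward and once censored at the last score. Results rest on 1,500 to 3,000 replicates and moved by up to about three percentage points between repeat runs.

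Rejection rate with no true effect (median 20 min in both arms):

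| Loss, KHJS v control | Carried forward | Censored |
|---|---|---|
| 10% v 10%, by 30 min | about 5% | about 5% |
| 2% v 5%, by 30 min | about 8% | about 5% |
| 5% v 15%, spread over the assessment grid | about 12% | about 5% |
| 5% v 15%, all by 30 min | about 27% | about 5% |

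If the 5% v 15% loss is uniform in clock time over 180 min, the carried-forward figure is about 7%. The assessment grid is denser early on, so loss spread over its points falls earlier than loss spread evenly over the clock.

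Power at the protocol's effect (10 v 20 min):

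| Loss, KHJS v control | Carried forward | Censored |
|---|---|---|
| 10% v 10%, by 30 min | about 96% | over 99% |
| 10% v 10%, spread over the assessment grid | about 99% | over 99% |
| 15% v 5%, uniform over 0–20 min | 42% | over 99% |
| 15% v 5%, uniform over 0–60 min | 89% | over 99% |
| 15% v 5%, uniform over 0–180 min | 99% | over 99% |

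**The case against.** The strongest reply is that early loss should be rare. The scores come from a supervised 3-hour hospital session, whereas treatment runs for up to 5 days and later scores are recorded at home. The withdrawal criteria include lack of improvement after 3 days and poor compliance, and a child lost on day 2 already has a complete primary outcome. The 10% allowance therefore cannot simply be placed in the first 30 min. A 5% v 15% split would mean 6 v 18 of 120 children gone within half an hour, which nothing in the protocol suggests. This stands, and it limits the size of the problem. The first half hour nevertheless matters most, because onset is expected at 10 to 20 min, and children may leave the study at any time.

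Three further points stand in part:
- Children with no post-dose score may not have the visit record needed for the full analysis set. Dropping them lowers the 5% v 15% early-loss figure from about 28% to 21% in the run where this was tested.
- Censoring looks clean here because loss was simulated as independent of onset. If children leave because they are not relieved, censoring is biased too.
- The article does not spell out how the carried-forward value enters the survival analysis. No onset to 180 min is the direct consequence of carrying the score, not the protocol's wording.

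A reader might infer that the rule biases the log-rank test in every case, or that the planned 10% loss costs the trial much of its power. The protocol supports neither. Equal loss leaves type I error at its nominal level and only attenuates a true effect. A large power loss (about 57% v 85%) appears only with a hazard ratio of 1.5 and all 10% lost by 30 min, and neither is the protocol's assumption.

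**Conclusion.** The point holds as a wrongly fixed rule of conditional size, and it should be fixed. Carry-forward does not suit a time-to-onset outcome and conflicts with the survival methods chosen for it. The direction is clear for the median (upward) and for equal loss (towards no difference). With loss that differs by arm, the error can go either way.

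The magnitude rests on the number of children lost before onset within 3 hours, which the protocol does not give. At 2% lost before any post-dose score the medians barely move, and at the protocol's assumed effect the power cost of equal loss is small. The material risk is unequal early loss, which cannot be excluded in advance. All test results assume exponential onset and non-informative loss.

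**What to change.** Replace the carry-forward sentence for the primary outcome with: *Children without onset are right-censored at their last WBS assessment, or at 180 min if assessed to the end.* Keep no onset to 180 min for lost children as a sensitivity analysis, because censoring assumes non-informative loss. The change should be made before the database is locked and treatment codes are opened, so that the choice cannot depend on the results. It costs one sentence plus one sensitivity analysis, with no new data and no change in sample size.

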### Ethical requirement

This study protocol has been submitted to the ethics committee of First Teaching Hospital of Tianjin University of TCM, the unit of clinical trial leader to get approval. It will also be submitted to other centers to get consensus. If there is any significant modification of the study protocol, the revised protocol, and the informed consent, CRF, researcher manual and other relevant documents involved in the modification should be resubmitted to the ethics committee for approval. The researcher conducting the study should be a senior attending physician or above and have received training in the relevant experimental techniques. In the event of injury or death related to the trial, the sponsor will be responsible for the treatment costs and financial compensation. Children who have not been cured after the end of the trial may continue to be treated by other medical methods at the expense of themselves. If the adverse reaction caused by the experimental drug occurs in patients during the trial, and the adverse reaction remains uncured after the end of the administration cycle, the sponsor shall bear the cost of treatment. Only the researchers and monitors involved in this trial have access to subject medical records, and the subjects’ data will not be used in other ancillary studies. The ethics committee and the pharmaceuticals supervisory and administrative departments shall have the right to consult the relevant research records of this project. In order to protect the privacy of the children during data processing, their identity information will be omitted. Both during and after the study, the subject medical records will be kept under strict security. Before screening, the researcher should explain the details of the project to the guardian and the child in plain language, so that they can fully understand and have enough time to consider. According to Article 20 of the *General Rules of the Civil Law of the People’s Republic of China*, “A minor who has not reached the age of eight yet is a person having no capacity for civil conduct and shall be represented in the performance of civil juristic acts by his or her agent ad litem”. All patients (≥ 8 years old) and their guardians should sign the informed consent before entering the study, and children under 8 years old should sign the informed consent by their guardians. Researchers should make children aware that participation is entirely voluntary and that they have the right to withdraw from the study at any time. The study protocol is based on the SPIRIT checklist [25]. The results of this study will be submitted to peer-reviewed journals.

## Discussion

TCM has a long history and has advantages in the treatment of many diseases, but it is not recommended by the international medical community due to the lack of evidence in related fields. After literature search and analysis, we found that the previous randomized controlled trials of Chinese patent medicine sprays used in children with acute pharyngitis/tonsillitis had poor methodological quality. KHJS has been on the market in China for more than a decade and has been widely used in the treatment of clinical throat diseases. We designed the prospective, multicenter, randomized, double-blind, parallel-group, placebo-controlled trial with the characteristics of TCM to determine the clinical positioning of KHJS through evidence-based research. After the high-level design meeting and feasibility study meeting held by multidisciplinary experts including pediatricians, statisticians, and methodology experts, the trial plan was finally formulated.

To our knowledge, this will be the first clinical trial to explore the immediate analgesic efficacy of a Chinese patent medicine spray for acute pharyngitis/tonsillitis induced sore throat in children in a multicenter, randomized, double-blinded, parallel-group, placebo-controlled manner. This study can not only prove the efficacy and safety of KHJS in the treatment of sore throat caused by acute pharyngitis/tonsillitis in children, but also provide evidence for the treatment of acute sore throat with Chinese herbal medicine.

Considering that throat sample culture is not routinely used in outpatient practice and may increase barriers to study entry, we did not take this method in this trial plan. Compared with using positive drug as control, choosing placebo as control can better test the absolute efficacy and safety of experimental drug in a randomized controlled trial. However, in clinical trials of Chinese patent medicines, especially liquid compounds, it is difficult to develop placebos that match the color, smell and taste of the experimental drugs. In order to better implement the blind method, we refer to relevant research data [26] and finally use 5% of the total dose of KHJS solution as placebo, but this method may interfere with the safety evaluation to some extent.

## Trial status

Protocol version 1.0, 15 January 2020. Recruitment is scheduled to occur from June 2020 until December 2020.

## Data Availability

The results will be published in a peer-reviewed journal and poster or presented orally at conferences. Data sets generated or analyzed in this study will be provided by the corresponding authors upon reasonable request.

## Abbreviations

KHJS: Kai-Hou-Jian spray (children’s type)
TCM: Traditional Chinese medicine
WBS: Wong-Baker FACES Pain Rating Scale
CRF: Case report form
AEs: Adverse events
NMPA: National Medical Products Administration
CRC: Researchers or clinical research coordinator
FAS: Full analysis set
PPS: Per-protocol set
SS: Safety set
95%CI: 95% confidence interval
